#### Sample size

A recruitment target of 80 male hockey fans of the London Knights and Sarnia Sting (40 per team; 20 men per arm within each team) was based on a sample size calculation for a subsequent full-scale RCT, following methods by FFIT [15]. To detect a 5 % difference in weight loss between intervention and comparison groups at 12 months, with a standard deviation of 19.9 %, 80 % power and a 0.05 two-sided significance level, 250 men are required in each arm [50]. To allow for 25 % loss to follow-up, a very conservative estimate, the sample size was increased to 335 men in each arm. A target of 670 men reflects the need to recruit 40 male hockey fans from 17 different OHL teams. The need to recruit 40 male hockey fans per site is reflected in this pilot trial.

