#### Randomization, allocation & blinding

Following baseline measurement (including seven days of tracking steps via a pedometer), participants returned for an enrolment and allocation session. The randomization sequence was computer-generated [1:1 in block sizes of 4 and stratified by site (London or Sarnia), using SAS version 9.4 (SAS Statistical Analysis Software)] and concealed using opaque envelopes until interventions were assigned (by an individual not involved in generating the randomization sequence). Participants were allocated in correspondence to the numerical order of the randomization envelopes and their order of appointments.

All participants (intervention and comparator) were provided with copies of Canada’s Food Guide [48] and the Canadian Physical Activity Guidelines [49]. All participants were also given an adverse events log and the research team member allocating participants stressed the importance of keeping the research team and/or their Hockey FIT coach informed of any injuries, illnesses, or changes in medication for the entirety of the study. Participants allocated to the intervention group were informed to keep their pedometer for use over the duration of the program. Participants allocated to the comparator group were asked to return their pedometer and continue with usual activities, without further intervention from the research team. Following completion of the 12-week measurement sessions, participants in the comparator group were invited to take part in the Hockey FIT program, following the exact same protocol as the intervention group.

Due to the nature of the study, participants and coaches could not be blinded to group allocation. During 12-week measurement sessions, a blinded assessor conducted all weight measurements in a separate room; no other measurements were blinded.

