#### Statistical analysis for outcome evaluation

For all outcome measures, observed values at baseline and 12 weeks will be summarized descriptively for each group. In addition, for the Hockey FIT group only, observed values at 12 months will be summarized descriptively. For data (average steps/day), participants were required to have at least three complete days of data, in order for data to be utilized in analyses [66].

Analyses will be performed following intent-to-treat principles; thus, we will include all participants with at least valid baseline data according to the randomization scheme and regardless of compliance with the intervention and data at follow-up. We will analyze data using mixed models for repeated measurements; linear mixed models will be used for continuous outcomes and generalized linear mixed models will be used for categorical and discrete outcomes. We will follow recommendations of Fitzmaurice et al. [67] and retain the baseline outcome as part of the outcome vector and constrain the group means as equal because of randomization. For all models, we will examine differences between groups at 12 weeks and changes within groups from baseline to 12 weeks (and to 12 months for the intervention group).

Terms included in models will include time, group (treatment) × time, age and site. Time will be modeled categorically with indicator variables (with baseline as the reference category). Residuals from models will be examined and subject to assumptions checks.

Based on our past experience, we do not expect substantial missing data; nonetheless, results will be valid provided data are missing at random and no imputation of data will be required by using a mixed model analysis approach [67]. To address participant dropout, we will also compare baseline characteristics of men who dropped out versus men who were included in the analysis. Interpretation of study results will primarily be based on estimation and associated 95 % confidence intervals. Two-sided *p*-values less than 0.05 will be reported as statistically significant. Analyses will be performed using SAS version 9.4 (SAS Statistical Analysis Software).

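### Site and age are listed only as effects common to all visits, so differences in 12-week change by site or age are largely left unadjusted (low severity, nearly free to fix)

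*Protocol article*

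**What the plan says.** Under *Statistical analysis for outcome evaluation*, the Protocol article sets out a constrained longitudinal model. It will "retain the baseline outcome as part of the outcome vector and constrain the group means as equal because of randomization". On time coding it says: "Time will be modeled categorically with indicator variables (with baseline as the reference category". The model terms are: "Terms included in models will include time, group (treatment) × time, age and site". The only interaction in that list is group by time, so age and site read as main effects.

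The targets are stated as: "we will examine differences between groups at 12 weeks and changes within groups from baseline to 12 weeks". The model classes are: "linear mixed models will be used for continuous outcomes and generalized linear mixed models will be used for categorical and discrete outcomes".

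Under *Randomization, allocation & blinding*, allocation is "1:1 in block sizes of 4 and stratified by site (London or Sarnia"). The *Sample size* section gives the planned layout as "40 per team; 20 men per arm within each team", that is, 80 men.

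**The concern.** When baseline is one of the outcomes, a main effect of site or age moves the baseline mean and the 12-week mean by the same amount. The model can then describe sites or ages that differ in level, but not sites or ages that differ in how much men change. For a strongly tracking outcome such as weight, the 12-week treatment contrast is in effect a contrast of changes, and the listed covariates have little to act on.

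Three things are at stake:
- **Interval width.** The article says interpretation will rest mainly on estimates and 95% intervals. If change differs by site, that variation stays in the model's residual although the design has balanced it across arms, and the intervals come out too wide.
- **Precision with respect to age.** Age is not balanced by design. An age effect on change adds real variability that the listed model does not remove.
- **Missing data.** The article relies on a missing-at-random argument, which also needs a correct mean model. If dropout depends on site and arm and site affects change, the listed mean model is not correct.

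**Working it through.** **Inputs.** From the article: 80 men, 1:1, stratified by site, 20 per arm per site, and the model terms above. It gives no baseline-to-12-week correlation, no SD for change and no site or age effect. Assumed here, for weight: baseline SD 18 kg; change independent of baseline with residual SD 4 kg; site difference in 12-week change d = 2, 3 or 4 kg; age effect on change a = 1 or 1.5 kg per SD of age. The article states no figure for this model that could be reproduced.

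**Step 1: what the listed model implies.** For the linear models, E[Y12 − Y0] = time effect + treatment effect. Site and age do not appear.

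**Step 2: what remains of a visit-constant effect.** Because baseline group means are constrained equal, the estimator is ANCOVA-like: (difference at 12 weeks) − β × (difference at baseline). A site effect s present at both visits therefore enters with weight s(1 − β). With equal SDs at the two visits, β equals the correlation, and the weight is 0.5s at 0.5, 0.3s at 0.7 and 0.05s at 0.95.

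Simulations with forced site imbalance (24/16 against 16/24), a 1 SD site effect and a true treatment effect of 0 gave these mean estimates:

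| Site effect | Correlation | Site omitted | Site main effect | Site × time |
|---|---|---|---|---|
| Both visits | 0.5 | −0.081 | 0.000 | 0.000 |
| Both visits | 0.95 | −0.010 | −0.002 | −0.002 |
| 12 weeks only | 0.5 | −0.193 | −0.135 | 0.005 |
| 12 weeks only | 0.95 | −0.202 | −0.188 | −0.001 |

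The main effect deals with a constant site effect. It deals poorly with one that acts on change.

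**Step 3: standard error, site effect in both arms.** Under the weight assumptions β = 1, so a main effect recovers nothing. With site × time the residual variance is 4² = 16. Without it the variance is 16 + d²/4. The ratio of standard errors is √((16 + d²/4)/16):
- d = 2: √(17/16) = 1.031 (simulated 1.041)
- d = 3: √(18.25/16) = 1.068 (simulated 1.077)
- d = 4: √(20/16) = 1.118 (simulated 1.127)

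The simulated ratio with no site effect is 1.007, which accounts for the small gap.

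The actual variability does not rise, because stratified blocks remove site from the contrast: 4 × √(4/80) = 0.894. At d = 4 the model reports 0.894 × 1.118 = 1.00 (simulated 1.00 against a true SD of 0.90).

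**Step 4: site effect in the intervention arm only.** The unadjusted variance is 16 + d²/8. With site × time it is 16 + d²/16. At d = 4: √(18/17) = 1.029 (simulated 1.034).

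**Step 5: age.** An age effect of a kg per SD adds a² to the variance, and blocking does not remove it. For a = 1, √(17/16) = 1.031; for a = 1.5, √(18.25/16) = 1.068. Unlike the site effect, this is a loss in the estimator itself: one simulation with an assumed age effect gave an empirical SD of 0.970 as planned against 0.939 with the interactions (0.970/0.939 = 1.033). With site and age together (2 kg and 1 kg; 3 kg and 1.5 kg), the simulated standard-error ratios were 1.070 and 1.142.

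**Step 6: dropout.** Suppose 40% drop out in one site's intervention arm and 5% in the other three cells. Expected completers are 12 and 19 in the intervention arm, and 19 and 19 in the control arm. That site then makes up 12/31 = 0.387 of the intervention arm and 0.5 of the control arm, a shift of −0.113. The bias is about −0.113 × 2 = −0.23 kg or −0.113 × 4 = −0.45 kg. Simulations gave −0.23 to −0.25 kg and −0.46 to −0.52 kg. With site × time the bias was near zero.

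**The case against.** The strongest reply is that this costs little and may cost almost nothing.

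- **The site term is not idle.** A reader might infer that site and age cancel altogether, so that the stratification factor goes unadjusted. That is too strong. It would hold for a change-score analysis or for β = 1. The article's constraint makes the estimator ANCOVA-like, and a visit-constant effect is adjusted with weight 1 − β. Steps, diet, alcohol and the psychological scores may well track baseline less closely than weight, and then the main effects do more. The algebra also does not carry over directly to the generalized linear mixed models. This stands.
- **Coaches and venue reach only the intervention arm during the 12 weeks.** Differences of that kind are site-by-treatment effects, for which the standard-error gain is only about 3–4% even at 4 kg. Only something like town or calendar time could act on both arms, and the article gives no reason to expect 2–4 kg from it. This stands and lowers the likely size.
- **For site, the estimator is no less precise.** Empirical SDs, planned against interacted, were 0.887 and 0.899 (2 kg), 0.883 and 0.890 (3 kg), and 0.912 and 0.922 (4 kg). The harm is a conservative standard error, with no inflation of type I error. This stands for site but not for age.
- **Little missing data is expected**, and a comparison of dropouts with those analysed is planned. The dropout bias is therefore a conditional risk. The planned comparison would describe such a pattern but would not correct for it.
- **The list of terms may not be exhaustive**, and a separate analysis plan is not shown. The sentence does, however, name its one interaction explicitly, so reading age and site as main effects is the natural reading.
- **This is an 80-man pilot** with nothing confirmatory resting on it. This stands and limits the severity.

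**Conclusion.** The point holds in a limited form. In the linear models as listed, differences by site or age in change from baseline to 12 weeks are largely unadjusted, most nearly completely for outcomes that track baseline closely.

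A reader might infer that the planned analysis is biased or invalid. The documents do not support that: randomization is blocked and stratified by site, so with complete data the estimate is unbiased, and for site its true precision is essentially unaffected.

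What remains is:
- a reported standard error about 4–13% too large if 12-week change differs by 2–4 kg between sites in both arms, or about 3–4% if 4 kg applies to the intervention arm only;
- a modest real loss of precision if age affects change;
- a bias of roughly a quarter to half a kilogram if heavy dropout falls in one site-by-arm cell and change differs by 2–4 kg between sites.

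All of these rest on assumed SDs and on assumed site, age and dropout effects, none of which the article gives. The weight calculations also use β = 1, the case least favourable to the planned model. Simulations at correlation 0.95 with a 0.5 SD site effect and a 0.3 SD age effect present only at 12 weeks gave a 56% larger standard error (0.106 against 0.068). For weight with an SD of 18 kg, that site effect would mean 0.5 × 18 = 9 kg between sites, so the figure should not be read as realistic. Severity is low.

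**What to change.** In the linear models, list the terms as time, group × time, age, site, age × time and site × time, and keep the equal-baseline constraint between groups. Centre age and code site symmetrically, so that the time terms still describe average within-group change. The 12-week treatment contrast keeps its meaning.

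The cost is two extra parameters for the 12-week comparison (two more for the 12-month visit if it is in the same model) and no new data. With no site or age effect on change, the standard error was essentially the same (0.875 as planned, 0.870 with the interactions). In the site-effect simulations the empirical SD rose by about 1% at most (for example 0.899/0.887 = 1.014). For the generalized linear mixed models the same terms can be considered, but the sizes given here were not derived for them. If the full-scale trial across 17 teams reuses this model, settling the wording now avoids carrying the gap forward.

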### Aims 3–5: Feasibility of recruiting and retaining overweight or obese men, acceptability of Hockey FIT program and research procedures, and Hockey FIT program optimization

#### Process evaluation data sources

Process data will be collected through self-reports, interviews, observation, questionnaires, and focus group discussions.

##### Participant self-reports at screening and information from baseline measurement sessions

Potential participants were contacted by the research coordinator and screened via email or phone to assess initial eligibility including: gender, age, height, weight, and how they heard about the Hockey FIT program. If the potential participant was deemed “likely” to be eligible after this stage, they were invited to a formal in-person screening session. Once registered in the program, participants attended a baseline measurement session, and demographic information was gathered such as age, postal code, marital status, education, occupation, and ethnicity, overall self-rated health, and clinical characteristics (described in greater detail in the outcome measures section above). These measures were collected to compare the demographics and health of the Hockey FIT participants to the health of men in the general Canadian population.

##### 12-week non-completer telephone interviews

Non-completers were defined as participants randomized to the intervention group who attended less than six program sessions (<50 %) and did not attend any of the final six program sessions.

Non-completers were contacted after all 12 sessions were completed and were asked to complete a program exit survey over the phone. Participants were asked about why they initially joined the program, why they stopped attending the program, if their involvement in the program has changed their lifestyle habits, and if (and how) the program could be changed to encourage them to complete the program.

##### Weekly attendance records

Hockey FIT coaches took attendance at the beginning of each of the 12 weekly sessions for both sites.

##### Fidelity (Program observations and post session coach reflections)

A member of the Hockey FIT research team was trained to observe program delivery at both London and Sarnia sites. All 12 weekly sessions at both sites were observed and notes were taken during the sessions. These notes detailed the overall session flow (completion of key tasks, classroom setup, interaction among participants, timing, style and method of delivery, and key lessons learned) and were summarized by the central research team. The research team member who observed the program delivery interviewed coaches after each session. Questions were specific to the experience delivering the program components and were standardized to what went well with delivery and what could be done differently.

##### 12-week participant program questionnaire

Participants randomized to the intervention group who had attended a minimum of six Hockey FIT coaching sessions (50 %), including at least one of the sessions in the final six weeks of the intervention were asked to complete a 12-week online questionnaire. The program questionnaires, created through the Qualtrics® platform, were e-mailed to participants via an individual link immediately following the final program session. A reminder was sent to men who had not completed the questionnaire after the final session. Questions explored reasons for joining, usefulness of program components, experience with the program and coaches, and any suggestions for improvement.

##### 12-week participant focus groups

At both sites, participants randomized to the intervention group were asked during sessions 11 and 12 to sign-up for a pre-determined focus group time slot. Focus groups were audio-recorded, semi-structured in nature, and moderated by a trained qualitative interviewer at both sites. Questions explored participants’ reasons for joining the program, experience with the program and health behaviour changes, and suggestions for future program improvement. Along with the interviewer, there was also an observer who made notes about group interactions, dynamics and flow of the focus group discussion. Focus groups were an hour and a half in length and the men were provided with healthy snacks, beverages and water bottles as a token of appreciation.

##### 12-week coach interviews

The four coaches (two Head Coaches and two Assistant Coaches) participated in one-on-one interviews by a trained qualitative interviewer. Questions were semi-structured and allowed for elaboration on key components of the program such as the strengths and weaknesses of the program, program delivery, and any suggested changes to the program.

##### 12-month participant program questionnaire

During the 12-month measurement session, intervention group participants were asked to fill out a questionnaire detailing their overall experience with the program and their experience with maintaining their healthy lifestyle behaviours, including use of eHealth technology support tools, following the active phase of the program. Participants were also asked whether they would recommend the program to others.

##### 12-month participant interview

All willing intervention group participants were interviewed one-on-one with trained qualitative researchers either in-person or via the telephone. Participants were asked about their experience maintaining behaviour changes made during the program, satisfaction with support from Hockey FIT staff and coaches, effectiveness of maintenance resources (Hockey FIT Social Network, Health*e*Steps app, and reunion/ booster session), and suggestions on how to improve the program.

#### Process evaluation & program optimization

These data sources will be analyzed to measure program reach, the reasons participants stayed with or opted out of the program, the extent to which coaches delivered Hockey FIT as designed, participants’ experiences of taking part in Hockey FIT, the coaches’ experience of delivering Hockey FIT, and the participants’ experience maintaining their lifestyle changes. Table 4 provides an overview of which data sources will address each process measure. The research team will track recruitment methods and reasons for study exclusion in order to address the feasibility of recruiting overweight and obese, middle-aged male hockey fans into a program focused on physical activity, exercise and healthy eating, delivered in collaboration with their favourite OHL team by trained Hockey FIT coaches. Acceptability of randomization will be estimated from the percentage of eligible men attending baseline measurements who gave informed consent to take part in the pilot trial. The research team will use findings from the process evaluation to inform program optimization.

**Table 4 Tab4:** Data sources to address process measures

Process measures	Data sources
Program Reach	Participant Self-Reports at Screening and Information from Baseline Sessions 12-Month Participant Program Questionnaire 12-Month Participant Interview
Reasons Participants Stayed With/Opted Out of the Program	12-Week Participant Focus Groups Weekly Attendance Records 12-Week Non-Completer Telephone Interviews 12-Month Participant Program Questionnaire 12 month Participant Interview
Extent to which Coaches Delivered Hockey FIT as Designed	Fidelity (Program Observations and Post Session Coach Reflections) Weekly Attendance Records 12-Week Coaches Interviews
Participants’ Experience of Taking Part in Hockey FIT	12-Week Participant Focus Groups 12-Week Participant Program Questionnaire 12-Month Participant Program Questionnaire 12-Month Participant Interview
Coaches’ Experience of Delivering Hockey FIT	12-Week Coaches Interviews Fidelity (Program Observations and Post Session Coach Reflections)
Participants’ Experience Maintaining Lifestyle Changes	12-Month Participant Program Questionnaire 12-Month Participant Interview

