**Fig. 1 Fig1:**
[figure not shown]
Flow Diagram for the Hockey Fans in Training Pilot Pragmatic Randomized Controlled Trial

Study recruitment began in April 2015 and the intervention periods started on May 12, 2015 (London site) and May 27, 2015 (Sarnia site). Western University Health Sciences Research Ethics Board approved this study and all participants provided written informed consent. The pRCT portion of this study was registered on February 26, 2015 with ClinicalTrials.gov (identifier: NCT02396524).

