#### Screening

The formal screening process for each man lasted approximately 20 min. Screening only proceeded once participants provided written informed consent to participate in the study. Following this, men self-completed the PAR-Q; if a participant answered, “yes” to one or more of seven questions on the PAR-Q, a research team member completed a Health Care Provider Clearance form to highlight specific concerns regarding the man’s ability to perform physical activity. This form was then provided to the Study Physician and Principal Investigator who determined whether the individual was cleared to participate in Hockey FIT. To conclude the screening session, participants were taken individually to a private area for measurements of height (Seca 213 portable stadiometer) and weight (Tanita HD351 digital weight scale). All eligible men were then invited to continue with a baseline measurement session.

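### The measure of acceptability of randomization equals 100 % by construction as written, because consent is taken before the baseline visit that defines its denominator

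*Protocol article*

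**What the plan says.** The measure is defined in the protocol article under Process evaluation & program optimization. Acceptability of randomization is the "percentage of eligible men attending baseline measurements who gave informed consent to take part in the pilot trial".

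Three other places fix the order of events:

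- Screening: "Screening only proceeded once participants provided written informed consent to participate in the study". The PAR-Q, height and weight follow. The section closes by inviting the men found eligible to baseline, so only men who have signed get that far.
- Randomization, allocation & blinding gives the next step: "Following baseline measurement (including seven days of tracking steps via a pedometer), participants returned for an enrolment and allocation session". The section mentions no consent at that visit.
- Study design, in the text after the Fig. 1 caption: "all participants provided written informed consent". No separate consent to the randomized part is mentioned.

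Aim 4 in Study aims covers acceptability of the research procedures as well as of the program.

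**The concern.** A percentage is informative only if some members of its denominator can fail to be in its numerator. Here that would require men who attended baseline without having consented, and the Screening section does not allow for any.

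The pilot is meant to support a full-scale randomized trial with a target of 670 men from 17 teams. Willingness to be randomized, with a 12-week wait for half of the men, is something such a pilot should be able to measure. A figure that must be 100 % would read as reassurance while being unable to show a problem.

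Little else in the article fills the gap. The non-completer interviews, the 12-week questionnaire, the focus groups, and the 12-month questionnaire and interviews are all confined to the intervention group. The comparators, who have most reason to be unhappy with their allocation, are not asked. Table 4 has no row for randomization.

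**Working it through.** The article gives no value for this measure, so there is no figure to reproduce. The check is on the order of events.

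**Order in the article**

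1. Written consent to the study (Screening).
2. PAR-Q, height and weight, and so eligibility (Screening).
3. Invitation to baseline, for eligible men only (Screening).
4. Baseline measurement with seven days of pedometer tracking (Randomization, allocation & blinding).
5. Return visit for enrolment and allocation (same section).

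**The measure**

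Let B be the eligible men who attended baseline and C the men who consented. The measure is |B ∩ C| / |B|. A man reaches step 4 only through step 1, so B is a subset of C. Then |B ∩ C| = |B|, and the ratio is 1 for any number attending.

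**Where reluctant men end up**

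| When he declines or leaves | In denominator? | In numerator? |
|---|---|---|
| Before or at consent | No | No |
| Between baseline and allocation | Yes | Yes |
| On learning his arm | Yes | Yes |

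None of the three can lower the percentage.

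**Comparison with a measure that can vary**

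Take the recruitment target of 80 (Sample size) as the number randomized. The numbers attending baseline below are assumed, because the article gives none.

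| Attended baseline (assumed) | Measure as written | Randomized / attended |
|---|---|---|
| 80 | 80/80 = 100 % | 80/80 = 100 % |
| 85 | 85/85 = 100 % | 80/85 = 94.1 % |
| 90 | 90/90 = 100 % | 80/90 = 88.9 % |
| 100 | 100/100 = 100 % | 80/100 = 80.0 % |

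**Effect of the recruitment target**

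The last column is not yet a clean measure, because the target limits how many men can be randomized. If 100 attended and 20 were turned away only because places were full, nobody refused, and the proportion is 80/(100 − 20) = 100 %. If 10 of the 20 were turned away for that reason, it is 80/(100 − 10) = 88.9 %. Men turned away only because places were full must therefore leave the denominator.

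**The case against.** The strongest reply is that the two consents may differ. Screening speaks of consent to the study, while the acceptability measure speaks of the pilot trial. The article treats the study as wider than the trial, since it also contains a process evaluation. The visit after baseline is called an enrolment and allocation session, so a trial-specific consent may have been taken there and lost in condensing the protocol. That would make the measure informative. The possibility stands as a reason to ask, but the article describes no such consent. Even if there was one, the reader cannot tell which consent is counted.

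A second reply takes all eligible men as the base and baseline attendance as part of the numerator. The result could then fall below 100 %. This is not the natural reading, and the figure would describe attendance at baseline, not acceptance of randomization.

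Third, loss after allocation is partly covered elsewhere. Retention for measurement sessions is part of Aim 3, all randomized men are contacted at follow-up, and dropouts are compared with the men analyzed. This is fair, but none of it reaches men who decline before allocation.

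Three stronger readings are tempting, and the article does not support them:

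- That this percentage drives a go/no-go decision. The article has no such rule or threshold. It says only that a larger trial is intended if the pilot is promising.
- That men who leave on learning their arm drop out of the measure. They stay in it and count as consenting.
- That randomized men divided by all men eligible at screening would show the true level of refusal. That ratio also absorbs baseline no-shows, pedometer burden, scheduling and the 80-man target.

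**Conclusion.** The concern holds. On the natural reading the measure is fixed at 100 % with no sampling variation, so it cannot detect unwillingness to be randomized. This rests on one assumption: that the consent described under Screening is the only one, as the article's text indicates. How far the true figure lies below 100 % cannot be derived from the article, and the percentages in the comparison table are illustrations only.

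The consequence is limited to a descriptive process measure under Aim 4 and to its use in planning the full-scale trial. No outcome analysis is affected.

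**What to change.** Reconcile the Screening section with Process evaluation & program optimization. If a separate consent to the trial was taken after baseline, state when, and say that this is the consent counted. Otherwise make three changes:

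1. Replace the measure with the proportion of eligible men attending baseline who return to the allocation session and accept randomization, with an exact 95 % confidence interval. Exclude from the denominator men not randomized only because the recruitment target was reached.
2. Report withdrawals at or after allocation by arm, next to 12-week retention by arm.
3. Report refusals at pre-screening or consent that were due to randomization or the wait-list, where reasons were recorded. The article mentions tracking recruitment methods and reasons for exclusion, but not reasons for refusal, so this item may be incomplete and should be labelled so.

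The estimate is still described in the future tense, so the wording can be changed, although recruitment and allocation are described as done and only what was recorded can be used. The cost is one reworded sentence, a few counts from screening, allocation and attendance records, and a figure that may be less favourable than 100 %.
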